### Participants

Inclusion criteria for participants will be (a) aged 65 years and above; (b) living in the community independently; (c) absence of diagnosed cognitive impairment; and will have (d) no participation in a structured PA program for two years preceding the study; and (e) passing score on the Timed-up-and-go test (TUG) and Abbreviated Mental Test (AMT). The TUG [23] and the AMT [24] are to assess participant’s physical competence and cognitive functioning, respectively. Participants i) whose time exceeds 20 s on the TUG or ii) whose AMT score is less than 6 or iii) who exhibit steady hypertension (160/90 mmHg or above), arthritis, and/or neurological disorders, will be excluded from the study.

### Sample size calculation

We computed a projected sample size using a statistical power analysis by G power [25]. The analysis was based on effect size (Cohen’s d = 1–1.88) from a previous study showing significant improvement in functional fitness (Cohen’s d = 1.88) and physical activity enjoyment (Cohen’s d = 1) following a LVB intervention, a control, and a comparison group [17]. With a more conservative effect size (Cohen’s d = .5), a total sample of 237 older adults is required in this three-group design study in order to achieve a power of 80% at a significance level of 5%. Finally, we aim to recruit 315 participants (45 participants per center, 7 elderly centers are needed, 105 participants in each group) in total, with a 25% expected dropout rate [26].

### Recruitment and procedures

Participants will be recruited via a presentation offered by the research team and via advertisements in the local neighborhood elderly centers (NECs). An information session (e.g., aims and procedures of the intervention) will be delivered to groups of potential participants. Participants will be advised of the confidentiality of personal data and informed that they can voluntarily withdraw from the project at any time without prejudice. Upon agreement from participants, data collection will be conducted in person by a research assistant and trained student helpers after obtaining informed consent. At the first testing session, participants will do the screening test (i.e., TUG, AMT). Prior to the physical measures (pre-test), participants will complete the questionnaires, socio-demographic questions, height, weight and percentage of body fat using a Tanita machine (model: TBF-410GS). Participants will then take the functional fitness tests in the standardized order used in Leung et al. [17]. The intervention will begin in the second week and continue as described. Participants will complete the post-test (same as the pre-test) within 7 days of following the 16 week (4 months) intervention. As suggested by Fjeldsoe et al. [27], two follow-up tests will be done 6 months and 12 months after completion of the intervention. All participants will receive a HK$100 (US$12) supermarket cash voucher as incentive for their participation. *See Fig. 1 for the design of the study using the CONSORT guidelines for RCT.

**Fig. 1 Fig1:**
[figure not shown]
Design of the study with CONSORT guidelines of RCT

### Measures

#### Physical attributes

##### Functional fitness

The Senior Fitness Test Manual [28] will guide the measurement of physical attributes of the participants. The tests consist of seven items: chair stand test (lower body strength), arm curl test (upper body strength), chair sit and reach test (lower body flexibility), back scratch (upper body flexibility), 8-ft up-and-go test (agility and balance), 2-min step test (aerobic endurance), and body mass index (BMI; kg/m2). These tests were found to be reliable (ICC: .80–.98 for participants in trials) and valid through content, construct and criterion-related analyses [28].

##### Balance test

The Balance System SD (Biodex) will be used to measure balance ability of participants in our intervention study. This system has previously been used to assess balance in a group of Hong Kong Chinese older adults [29]. In the test, participants will be asked to maintain the vertical projection with their centre of gravity in the centre of the platform by observing a vertical screen located 30 cm in front of their face. Each assessment will take 20 s, with 10-s rest periods in between. The average of the results from three trials will be obtained. Reliability (test-retest reliability = .69–.80) and validity of the balance test was supported in the studies of Parraca et al. [30] and Finn et al. [31].

#### Psychological attributes

##### Resilience

The 25-item Resilience Scale (RS) [32] will be used to measure resilience (i.e., the outcomes of successful adaptation despite challenging or threatening circumstances of participants). This scale is reliable (test-retest reliability = .8; Cronbach’s α = .95) for Chinese elderly populations [33]. The exploratory principal component analysis also found that RS was valid in a four-factor structure.

##### Quality of life

Quality of life will be measured using the Chinese version of the Medical Outcomes Survey 36-Item Short Form Health Survey (SF-36) [34]. The reliability and validity of the SF-36 questionnaire have been confirmed for Chinese individuals [34]. This survey contains eight domains: physical functioning (PF), physical role, bodily pain, general health (GH), vitality, social functioning (SF), emotional role, and mental health. In the present study, only PF, SF and GH will be included in order to lower the participants’ burden to complete the questionnaires. Examples of the items include asking participants if they encountered any restrictions or limitations while performing moderate PA, such as moving a table, using a vacuum cleaner, bowling, playing golf, and walking. The score ranges from 0 to 100 and a higher score indicates better physical functioning.

##### PA enjoyment

The short version (8 items) of the PA Enjoyment Scale (PACES) [35], translated to Chinese, will be used to measure participants’ PA enjoyment throughout the study. The Scale was originally developed by Kendzierski and DeCarlo [36]. This short version the PACES questionnaire is a reliable and valid instrument for assessing PA enjoyment in Chinese older adults [35]. In specific, the test-retest reliability and internal consistency was moderate (intraclass correlation coefficient = 0.614) and high (Cronbach’s alpha = .91–.92), respectively. Its convergent validity was supported that PACES was moderately correlated with quality of life in older adults.

### Data analysis

Data will be analysed using SPSS 24.0 with a significance level of .05. To answer study objectives (a)-(c), generalized estimating equations (GEE) models will be used to analyse mean changes in outcomes over time among the three groups with adjustment for baseline characteristics showing statistically significant differences among the groups. GEE models was used in similar study such as Kekäläinen et al. [37] and it take into account the Intra-class correlation coefficient of responses within an elderly centre and correlations between repeated measurements in the same individual. In addition, the GEE models do not require complete data and can be fit even when individuals do not have observations at every time point. Descriptive statistics of the socio-demographic variables (e.g., frequency, M and SD) will also be computed.

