**Methods/design:**

This study will apply both quantitative and qualitative methods with a large sample (approximately 315 participants). We will adopt a randomized controlled trial (RCT) design to further evaluate the effectiveness of a LVB intervention on health outcomes against a comparison group, Tai Chi (TC), and a control group (C). Older adults will be eligible to join the intervention if they are (a) aged 65 years and above; (b) living in the community independently; (c) absent of diagnosed cognitive impairment; (d) not regular participants in a structured PA program for two years preceding the study; and (e) able to achieve a passing score on the Timed-up-and-go test (TUG) and Abbreviated Mental Test (AMT).

About 315 participants will be randomly assigned into 3 groups in 1:1:1 ratio. LVB group participants will receive 16-week LVB program; TC group will utilize a simplified 24-form Yang Style TC, and C group participants will be instructed to maintain their normal daily activity and join regular non-exercise social gatherings. Measurements will be collected before and after the intervention, and 6 months and 12 months after completion of the intervention.

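### Thirteen outcome scores are tested at a flat .05 with no primary outcome, no primary time point and no ranking of contrasts, so the overall false-positive risk is well above 5%

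*Protocol article*

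**What the plan says.** All references are to the protocol article.

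- **Outcomes.** Functional fitness: "The tests consist of seven items", of which BMI is one. Balance: "The Balance System SD (Biodex) will be used to measure balance ability of participants in our intervention study". Resilience: "The 25-item Resilience Scale (RS) [32] will be used to measure resilience". Quality of life, from the SF-36: "only PF, SF and GH will be included". Physical activity enjoyment is scored on the short PACES.
- **Visits.** "Measurements will be collected before and after the intervention, and 6 months and 12 months after completion of the intervention" (Abstract, Methods/design).
- **Analysis.** Under Data analysis, "generalized estimating equations (GEE) models will be used to analyse mean changes in outcomes over time among the three groups", and "Data will be analysed using SPSS 24.0 with a significance level of .05". No adjustment for multiple testing is mentioned.
- **Contrasts.** Objectives (a) to (c) compare LVB with TC. The hypotheses under Study design, repeated in the Discussion, predict that LVB and TC each improve selected physical and psychological attributes relative to control, and that LVB will do at least as well as TC.
- **Sample size.** Two pilot effects are cited (d = 1.88 for functional fitness, d = 1 for enjoyment). The calculation then uses d = .5 and gives 237 participants for 80% power at 5%, raised to 315 for 25% dropout. The outcome, contrast and visit to which the 80% applies are not stated.

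**The concern.** A trial with many outcomes can hold its error rate at 5% for its main claim only if that claim is fixed beforehand. Here the objectives name domains, and functional fitness alone is seven separate scores with no composite defined. The hypotheses speak of selected attributes without selecting any. A reader of the results could not tell which significant finding was the planned test and which was one of many.

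The power statement has the same gap: it describes a single test at 5%, yet the plan has no single test to which it belongs. The article says that a positive result is meant to inform public policy on exercise for older adults, so the strength of the main claim matters.

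**Working it through.** **Step 1. Count of scores.** From Measures: 7 fitness items + 1 balance + 1 resilience + 3 SF-36 domains + 1 enjoyment = 13. There are three arms, hence 3 pairwise contrasts, and 3 post-baseline visits (16 weeks, 6 months, 12 months).

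**Step 2. The plan's own sample size.** Take a one-way three-group F-test at .05, with d = .5 as the distance between the extreme means and the third mean midway. Then f = .5/√6 = .204. The noncentral F distribution gives power .805 at N = 237, and .7995 at N = 234, so 237 is the smallest balanced total that reaches 80%. Dropout: 237/.75 = 316, against 315 stated, a rounding difference. The figure is therefore reproduced as one omnibus test of one outcome at 5%.

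**Step 3. One group-by-time test per outcome.** This is the reading closest to the Data analysis section. With independent outcomes:

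1 − .95^13 = .49

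Outcomes in the same people are correlated, so this was also simulated under the global null (20,000 runs per setting, 13 outcomes, 3 visits, 3 arms, two-sided .05).

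| Correlation between outcomes | Chance of at least one false positive in 13 tests |
|---|---|
| 0 | .49 |
| .3 | .43 |
| .5 | .35 |
| .7 | .26 |

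**Step 4. If every pairwise contrast is tested at every visit.** 13 × 3 × 3 = 117 tests, and 117 × .05 = 5.85 false positives expected. The three contrasts share arms, and visits are correlated, so the chance of at least one was simulated.

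| Correlation between outcomes / between visits | Any false positive, 117 tests | False result favouring LVB over TC or control |
|---|---|---|
| 0 / 0 | .99 | .84 |
| .3 / .5 | .97 | .62 |
| .5 / .5 | .92 | .52 |
| .7 / .7 | .76 | .36 |

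An intermediate case, all three contrasts at the 16-week visit only (39 tests), gives .81 falling to .48.

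**Step 5. What the choice does to power.** With one prespecified test at .05, the error rate of that claim is .05 and the N = 237 calculation applies to it. If instead all 13 outcomes were to be confirmatory under Bonferroni (.05/13 = .0038), power per outcome at N = 237 falls from .80 to .47, and about 399 evaluable participants would be needed for 80%.

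**The case against.** The strongest reply is that the article condenses a fuller plan. Adjustment methods, visit-specific contrasts and the handling of secondary outcomes are commonly left to a statistical analysis plan, and their absence here is no defect. That stands for the choice of method. It does not cover the primary outcome: the article publishes a sample size with 80% power, and Step 5 shows that whether 237 is enough depends on how many outcomes carry the claim.

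Three stronger readings are tempting, and the article does not support them.

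- **That a false finding is close to certain.** This needs all 117 tests, low to moderate correlations, and any significant result in either direction counted as success. The analysis text describes change over time among three groups and specifies no such grid. Nor does the article define success as any one significant item.
- **That no contrast is given.** Contrasts are given. The objectives and hypotheses emphasise different ones, and none is made primary.
- **That outcomes will be picked after the data are seen.** Every instrument is listed in advance. The article leaves room for selection but does not show any intent to select.

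It is also fair to say that d = .5 lies below both pilot effects, so the 80% can be read as a per-outcome figure for either. The point that no outcome is named remains.

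**Conclusion.** The point holds in a limited form. Thirteen scores, three arms and three post-baseline visits share one .05 level, with no primary outcome, no primary time point and unranked contrasts. The stated power belongs to one unnamed outcome.

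On every reading computed, the chance of at least one false positive exceeds 5%: about 25–49% with one group-by-time test per outcome, and about 76–99% only if every contrast is tested at every visit. On that full grid, a false result favouring LVB has a chance of about 36–84%. Even the lowest figure is about five times the nominal level.

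These figures assume that no intervention has any effect, that tests are two-sided, and that correlations between outcomes and between visits lie between 0 and .7. The article gives no correlations. The counts and the missing hierarchy need no assumption.

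**What to change.** Before any unblinded analysis, state in the protocol and the registry entry:

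1. One primary outcome, either a single functional-fitness test or a composite with its formula.
2. The 16-week post-test as the primary time point.
3. One primary contrast, or a fixed order of contrasts, that agrees with both the objectives and the hypotheses. If LVB against TC is included, say whether it tests a difference or the expectation that LVB is at least as effective. The latter needs a margin, and a non-significant difference would not establish it.
4. That these are tested at .05 and that the sample-size statement refers to them by name.
5. That all other outcomes and visits are secondary, either adjusted for multiplicity or reported with 95% confidence intervals and no confirmatory claim.

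This needs no new data and no larger sample, provided the named primary test is powered by the existing calculation. If the primary contrast is pairwise rather than the three-group test, the calculation should be restated for it. The price is that fewer outcomes can be presented as confirmatory.

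### Each outcome's own pre-test value is adjusted for only if it happens to differ significantly between groups; always conditioning on it would sharpen the GEE contrasts at no cost

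*Protocol article*

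**What the plan says.** The quantitative Data analysis section states that "generalized estimating equations (GEE) models will be used to analyse mean changes in outcomes over time among the three groups", and the same sentence continues "with adjustment for baseline characteristics showing statistically significant differences among the groups". No outcome's pre-test value is named as a covariate, and none is excluded. The section does not say whether pre-test is one of the GEE responses, whether change scores are the response, or whether the groups share a common baseline mean.

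The pre-test values will exist for every outcome, because Recruitment and procedures says "Participants will complete the post-test (same as the pre-test) within 7 days of following the 16 week (4 months) intervention". Two further measurements follow, 6 and 12 months after the intervention ends.

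The article gives no pre-post correlation over 16 weeks or longer. It does give reliability figures. For enjoyment, "the test-retest reliability and internal consistency was moderate (intraclass correlation coefficient = 0.614"; for balance, "Reliability (test-retest reliability = .69–.80". Under Measures it also gives 0.8 (test-retest) for the resilience scale and ICCs of .80 to .98 for the functional fitness tests. No figure is given for the SF-36 scales.

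**The concern.** When an outcome is measured before and after treatment, its own baseline value is usually the strongest predictor of the later value. Comparing mean changes fixes the weight on baseline at 1, whereas conditioning on baseline estimates that weight from the data. With equal variances at the two visits, the change comparison is never the more precise of the two, and it loses most where the pre-post correlation is modest.

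A change comparison also carries regression to the mean. In any one trial, a group that starts lower by chance tends to show a larger change.

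The plan's safeguard is a significance test of baseline differences. In a randomised trial such a test rarely fires, so it leaves out a prognostic baseline nearly every time. At stake are precision that costs nothing to collect and the readability of a single trial's contrasts, including the comparison of LVB with TC.

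**Working it through.** **Inputs.** From Sample size calculation: d = .5, total 237, 80% power, 5% significance, 25% dropout. From Study intervention: 1:1:1 allocation, so 237/3 = 79 analysed per arm. Correlations (ρ) are the reliability figures listed above, used as proxies. Assumptions: equal variances at each visit, a linear relation between visits, and no allowance for clustering by centre.

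**1. The plan's own figure.** Take a three-group F test with means spread over d = .5 and the middle group midway. Then f = .5 × √(1/6) = 0.204, and the non-centrality is 237 × 0.204² ≈ 9.87. At α = .05 the power is 80.5%, and 237 is the smallest total with equal groups that reaches 80%. For dropout, 237/0.75 = 316, against the stated 315. The sample size stands.

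**2. What a change model estimates.** With complete visits, a GEE with pre-test as a response and group-by-time terms returned 0.4749 for the LVB-control contrast at post-test. The plain difference in mean change was also 0.4749.

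**3. Variance.** With unit variance at each visit:
- change: 1 + 1 − 2ρ = 2(1 − ρ)
- conditional on baseline: 1 − ρ² = (1 − ρ)(1 + ρ)
- ratio, adjusted to change: (1 + ρ)/2

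If d = .5 is in SDs of change, the results are:

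| Outcome | ρ | Ratio | Variance cut | 237 × ratio | Omnibus power at 237 |
|---|---|---|---|---|---|
| Change analysis | – | 1 | – | 237 | 80.5% |
| Enjoyment | 0.614 | 0.807 | 19% | 191 | 88.5% |
| Balance, lower value | 0.69 | 0.845 | 16% | 200 | 87.0% |
| Balance, upper value; resilience; fitness, lower value | 0.80 | 0.900 | 10% | 213 | 84.7% |
| Fitness, upper value | 0.98 | 0.990 | 1% | 235 | 80.9% |

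If the true correlations over 4 to 16 months are lower, say 0.3 to 0.6 (an assumed range), the variance cut is 35% to 20%.

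**4. Shift from chance imbalance.** A realised baseline difference D moves the change contrast by −(1 − ρ)D. At 79 per arm the SE of D is √(2/79) = 0.159 SD.
- D of 1 SE: 0.386 × 0.159 = 0.061 SD at ρ = 0.614; 0.20 × 0.159 = 0.032 SD at ρ = 0.80.
- D of 1.96 SE: 0.12 SD and 0.06 SD, about 24% and 12% of d = .5.

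**5. What the significance rule does.** In 4,000 simulated trials at each of ρ = 0.5, 0.614 and 0.8, with 79 per arm, the baseline test fired 4.6% to 5.3% of the time. At ρ = 0.614, treating a triggered covariate as fully effective:

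| Analysis | Mean estimate (true 0.50) | SE | Correlation with baseline difference |
|---|---|---|---|
| Change only | 0.50 | 0.138 | −0.44 |
| Significance rule | 0.50 | 0.135 | −0.36 |
| Always adjusted | 0.50 | 0.124 | about 0 |

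**6. Whether a triggered covariate works depends on the response.**
- *Pre-test as a response, group-by-time terms.* A person-level main effect moves all visits equally and cancels out of the change. In 100 runs at ρ = 0.614 the SE was 0.139 with or without the baseline main effect. With about 25% dropout it was 0.145 with and 0.144 without, and estimates differed by at most 0.027. Using post-baseline responses with baseline and baseline-by-time, the SE was 0.125 (complete) and 0.131 (dropout).
- *Change scores as the response.* In 40 runs at ρ = 0.6, adding the baseline covariate gave the same contrast as baseline-adjusted post-test scores, and the SE fell from 0.142 to 0.126.

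**The case against.** A reader might infer that the plan never conditions on baseline, and that its adjustment achieves nothing whichever covariates are chosen. The text does not support either. The analysis sentence goes on to allow adjustment for baseline characteristics that differ significantly, and a baseline outcome score could qualify. The adjustment is without effect only if pre-test is a response, the covariate enters as a main effect and visits are complete. The article states none of these and expects 25% dropout. If change is the response, a triggered baseline covariate works fully.

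A reader might also infer bias or a power shortfall. Neither follows. The mean estimate was 0.50 under all three analyses, so the shift in step 4 is conditional on the realised imbalance and already reflected in the change-score SE. If d = .5 is in post-test SDs, the change variance 2(1 − ρ) is at most 1 whenever ρ is at least 0.5. The change analysis then needs no more than 237, and every reliability quoted exceeds that value.

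It is also fair to say that a condensed article leaves the full model specification to an analysis plan, and that much of this is a covariate-selection point. Both are partly right. But the article does fix two things, the change target and the significance rule, and together they keep the baseline outcome out about 95% of the time. Dropping the rule alone would not be enough if pre-test stays a response with unconstrained group means.

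**Conclusion.** The point holds as one of efficiency. The plan targets mean change and does not prespecify conditioning on each outcome's own pre-test value. On either reading of the model this leaves precision unused: about 19% of variance for enjoyment, 10–16% for balance, 10% for resilience and 1–10% for functional fitness. For the most reliable fitness tests the gain is negligible.

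These figures treat quoted reliabilities as pre-post correlations, which they probably overstate over 4 to 16 months; lower correlations would make the loss larger. No estimate is possible for quality of life from the figures given. The contrast is valid, and the stated sample size and power stand. This is a free improvement rather than the correction of an error.

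**What to change.** In the quantitative Data analysis section, specify for every outcome, whatever the baseline tests show, a GEE whose responses are the three post-baseline visits (post-test, 6 months, 12 months). Its terms are group, time, group-by-time, the outcome's own pre-test value and pre-test-by-time. Report the adjusted group differences at each visit. Alternatively, keep pre-test as a response, constrain the three groups to a common baseline mean and use a working correlation other than independence. In either case, delete the rule that selects covariates by baseline significance.

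The cost is a few sentences and a different SPSS model specification, with no new participants, visits or measures. In the first form, participants with no post-baseline visit do not contribute; they supply no observed change under the present plan either.

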### Study intervention (objective #1–3)

In order to answer project objectives (a)-(d), the study will adopt a RCT. About 315 participants will be randomly assigned into LVB group, TC group and control group in 1:1:1 ratio; this will be about 103 participants in each group. Data will be collected at baseline (pre-test), after a 16-week intervention (post-test), and 6 months and 12 months after the intervention is completed. The intervention will be based on the previous program specifically designed for older adults in LVB [17] and in TC [18]. Each program consists of 32 training sessions, with 2 × 90-min sessions per week. The duration of the proposed intervention is consistent with the recommendation of U.S. Department of Health and Human Services (HHS) for PA recommendations [22]. The LVB Group’s program will be delivered by registered coaches from the Light Volleyball Association of HKG (LVBAHK). Content for this program is designed by the project co-ordinator (PC) and LVBAHK, which was found to be effective for improving health of older adults [17]. The TC Group will utilize a simplified 24-form Yang Style TC that is designed for easy learning and mastery. Participants will be led by a qualified TC instructor, and they will replicate instructor’s motions, postures, and movement speed. Any incorrect performance will be rectified by the instructor in the class. During the intervention, the control group participants will be instructed to maintain their normal daily activity and join regular non-exercise social gatherings in order to balance the psychosocial effect (i.e., to maintain the internal validity of the study) of regular gatherings for the LVB and TC groups.

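### Being able to fit GEE with missed visits does not make the 6- and 12-month contrasts unbiased when 25% dropout is expected; a likelihood mixed model or dropout-weighted GEE would be safer

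*Protocol article*

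**What the plan says.** The quantitative Data analysis section of the protocol article states that "generalized estimating equations (GEE) models will be used to analyse mean changes in outcomes over time among the three groups". It says these models "take into account the Intra-class correlation coefficient of responses within an elderly centre and correlations between repeated measurements in the same individual". It then adds, as a further merit of the method, that "the GEE models do not require complete data and can be fit even when individuals do not have observations at every time point". That is the article's only remark on missing outcomes in the analysis.

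The Sample size calculation section reads "With a more conservative effect size (Cohen’s d = .5), a total sample of 237 older adults is required", and sets a recruitment target of 315 "with a 25% expected dropout rate". The target is laid out as "45 participants per center, 7 elderly centers are needed, 105 participants in each group". Participants are "randomly assigned into LVB group, TC group and control group in 1:1:1 ratio", and outcomes are measured at baseline, after the 16-week programme, and 6 and 12 months after it ends.

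**The concern.** The remark on incomplete data is offered as a reason for choosing GEE, but it speaks to whether the model can be computed, not to whether the estimates are right. Recruiting 315 instead of 237 restores precision; it does nothing about bias from who leaves.

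Unequal dropout is plausible on the article's own account. The arms are a team sport, an individual exercise and non-exercise gatherings. The Study design section links social support to programme adherence and contrasts the team sport with individual Tai Chi. The qualitative section plans to interview light volleyball (LVB) non-completers. If people leave according to their earlier scores, and do so differently by arm, the participants still seen at 6 and 12 months are no longer comparable. Those follow-up contrasts are also what the Background section asks for beyond the pilot.

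**Working it through.** **1. The plan's own figures.** Inputs from Sample size calculation: three groups, d = 0.5, power 80%, significance level 5%, dropout 25%. The effect-size convention is not stated. Taking d between the extreme groups with the third midway gives f = d/√6 = 0.5/2.449 = 0.204. One-way ANOVA power (noncentral F) then gives N = 237 with power 0.805, an exact match. Inflation for dropout gives 237/0.75 = 316, against 315 stated (315 × 0.75 = 236.25). So 25% is a genuine planning input, and 237/3 = 79 per arm are expected to be evaluable.

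**2. Why the working correlation matters.** GEE solves Σ Xᵢ′Vᵢ⁻¹(yᵢ − μᵢ) = 0 over the visits observed, where Vᵢ is the working covariance. If V is independence and the model has a mean for each arm and visit, the 12-month estimate is the plain mean of those still attending. If leavers had lower earlier scores and visits are correlated, that mean is too high. If V matches the true covariance, a leaver's earlier visits carry the needed correction. With V near independence, they carry almost none.

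**3. Size with no true effect.** Assumptions, none given in the documents: four visits, SD 1, about 25% missing at the last visit in each arm, dropout in the LVB arm depending on the last observed score (logistic slope 0.5 or 1 per SD), dropout random in control. The true correlation is either exchangeable 0.6 or serial with lag-one 0.7. Large-sample bias of the 12-month contrast, in SD:

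| Slope, true correlation | Independence GEE | Person-level exchangeable GEE | Likelihood, unstructured |
|---|---|---|---|
| 0.5, exchangeable | 0.082 | 0.004 | 0.003 |
| 0.5, serial | 0.063 | −0.013 | −0.002 |
| 1, exchangeable | 0.144 | 0.000 | 0.000 |
| 1, serial | 0.125 | −0.017 | 0.001 |

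**4. The centre as the GEE cluster.** The article wants the model to reflect correlation both within centre and within person. If the centre is the cluster with a single exchangeable correlation, 45 people × 4 visits = 180 observations. Each is paired with 179 others, of which 3 belong to the same person: 3/179 = 1.7%. The fitted correlation then falls to about the centre intraclass correlation. With assumed values of 0.02 and 0.05 for that, simulation gave a fitted correlation of 0.03 to 0.06 and a 12-month bias of 0.05 to 0.10 SD (slope 0.5) and 0.12 to 0.14 SD (slope 1), with Monte Carlo error about 0.012. A large-sample check with the working correlation set at 0.05 gave 0.06 to 0.13 SD. This is nearly the independence result.

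**5. A second set of assumptions.** True effect 0.50 SD, 25% lost after the post-test, within-person correlation 0.5 / 0.7 / 0.8. Estimated 12-month effect:

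| Dropout mechanism | Independence | Correct exchangeable |
|---|---|---|
| Completely random | 0.50 / 0.50 / 0.50 | 0.50 / 0.50 / 0.50 |
| Same score dependence in both arms | 0.51 / 0.50 / 0.51 | 0.51 / 0.50 / 0.50 |
| Score-dependent in one arm only | 0.61 / 0.65 / 0.67 | 0.51 / 0.50 / 0.50 |
| Opposite directions by arm | 0.72 / 0.80 / 0.84 | 0.50 / 0.50 / 0.50 |

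**6. Scale.** With 79 per arm, the standard error of an unadjusted difference is about √(2/79) = 0.16 SD. A bias of 0.06 to 0.14 SD is 0.06/0.16 = 0.4 to 0.14/0.16 = 0.9 of a standard error. A bias of 0.02 SD is 0.02/0.16 = 0.1.

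**The case against.** The strongest reply is that the sentence is true as written. It claims neither lack of bias nor validity under MAR, and it does not mention dropout. A reader might infer that the plan claims GEE deals with the 25% dropout. The article never says so; that dropout figure appears only under Sample size calculation. This stands, and it is why the sentence should be qualified, not removed.

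Second, the working correlation, weights and sensitivity analyses are commonly left to an analysis plan, which is not shown. That also stands: their absence is not the point here. The point is the method named and the reason given for it, which does not support validity under dropout.

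Third, the larger biases need an independence or very weak working correlation, while the article says repeated measurements within a person are taken into account. A person-level exchangeable structure would leave at most about 0.02 SD. This is right and limits the point. It does not remove it, because the same sentence also asks for centre correlation, and clustering on centre alone brings the larger bias back.

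Fourth, score dependence in one arm only is an unfavourable assumption. With the same mechanism in both arms, bias is close to nil even under independence. That also stands.

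**Conclusion.** The point holds in limited form. The stated reason for GEE does not protect the 6- and 12-month contrasts against selective dropout. If dropout depends on earlier scores in one arm and is random in the comparator, the 12-month bias is about 0.06 to 0.14 SD under an independence or weak centre-level working correlation, at most about 0.02 SD under person-level exchangeable, and about zero under likelihood with unstructured covariance. The mechanism, correlations, centre intraclass correlation and timing of loss are all assumptions. The second set of assumptions gave larger shifts under independence: 0.11 to 0.17 SD for one arm (0.61 − 0.50 to 0.67 − 0.50) and 0.22 to 0.34 SD for opposite directions (0.72 − 0.50 to 0.84 − 0.50). The size therefore cannot be fixed from the documents.

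Three stronger readings are not supported. The first is that the bias will be 29% of the planned effect (0.144/0.5): that is the worst of the four cases in the first table, under independence. The second is that contrasts move toward the arm that loses its weaker participants: with exchangeable GEE and serial truth the sign reverses, so the direction cannot be known in advance. The third is that dropout is known to be MAR and not completely random: it is plausible, but the article gives no evidence either way.

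**What to change.** Analyse objectives (a)-(c) with a likelihood-based mixed model for repeated measures: unstructured within-person covariance, all randomised participants in their assigned arm, and a centre term. The centre term is needed because the article intends to account for centre and the within-person covariance alone does not.

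If GEE is kept, make the person the repeated-measures unit, use a non-independence working correlation, and apply inverse-probability-of-dropout weights.

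In either case, add one sensitivity analysis in which missing values are shifted by a stated delta, separately by arm. Keep the sentence on incomplete data, but state the missing-data assumption under which the estimates are valid.

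The cost is some wording in the Data analysis section and a little more analysis work, with no new data and no change to the sample size. The main analysis would still rest on MAR, which the data cannot confirm; the delta analysis shows how far the result depends on it.
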